## **1.2 Data management**

Study data will be entered directly into a secure web-based case report form with the option to print blank and completed forms. A detailed study monitoring plan will be prepared by the study management committee prior to commencement of the study. On site source monitoring will be conducted by the co-ordinating centre and will include 100% source data verification for the primary end point. Source data verification will be completed for all data points for the first two patients at each centre and for a random sample of patients during monitoring visits thereafter.

## **1.3 Records retention**

Once the study is completed, paper records will be shredded and electronic database will be destroyed 15 years after the completion of the study. Only authorised study personnel will have access to the electronic database. At the time of study completion, computer records will be copied to a compact disc for long term storage and back up.

## **METHODS: MONITORING**

### **Data monitoring**

#### **Data Monitoring Committee composition and governance**

An independent Data Monitoring Committee (DMC), consisting of experts in intensive care and rehabilitation will be established before patient enrolment.

#### **Interim analyses**

No interim analysis is planned. However, all SAEs will be provided to the DSMB and the DSMB reserves the right to call for a blinded or unblinded interim analysis at any point in the conduct of the trial.

### **Harms**

It is recognised that the intensive care patient population will experience a number of common aberrations in laboratory values, signs and symptoms due to the severity of the

underlying disease and the impact of standard therapies. Intensive care patients will frequently develop life-threatening organ failure(s) unrelated to study interventions and despite optimal management. Therefore, consistent with established practice in academic ICU trials, events that are part of the natural history of the primary disease process or expected complications of critical illness will not automatically be reported as serious adverse events in this study. All adverse events which are considered to be potentially causally related to the study intervention or are otherwise of concern in the investigator's judgement will be reported.

Potential side effects: Cardiac failure, Myocardial ischaemia, Virilisation in females (hoarseness, acne, hirsutism), abnormal LFTs, Polycythaemia, Increased sensitivity to oral anticoagulants.

Safety endpoints include: new onset hypertension (SBP>180units), abnormal liver function tests (ALT increase > 100% from baseline and >100), cardiac ischaemia or heart failure, virilisation in females.

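### The SAE carve-out does not set aside nandrolone's own named cardiac and liver harms, so their routine route to the DSMB depends on blinded, patient-by-patient judgement

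*Protocol*

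**What the plan says.** Three parts of the protocol bear on this point.

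- **Harms, reporting rule.** The section sets the background with "Intensive care patients will frequently develop life-threatening organ failure(s) unrelated to study interventions and despite optimal management". It then says that natural-history events and "expected complications of critical illness will not automatically be reported as serious adverse events in this study". The next sentence limits this: "All adverse events which are considered to be potentially causally related to the study intervention", or that are "otherwise of concern in the investigator's judgement will be reported".
- **Harms, named events.** The list of possible drug effects begins "Potential side effects: Cardiac failure, Myocardial ischaemia, Virilisation in females" and goes on to include abnormal liver function tests. The safety endpoints are new hypertension, a defined rise in ALT, and "cardiac ischaemia or heart failure, virilisation in females".
- **Interim analyses.** None is planned, but "all SAEs will be provided to the DSMB", and that board may ask for an analysis, blinded or by arm, whenever it chooses.

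The Study interventions section adds that investigators and treating staff do not know the allocation. The section on the monitoring committee's composition calls it a DMC and the Interim analyses section calls it a DSMB; they are read here as one body.

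**The concern.** A carve-out of this kind is reasonable in intensive care, where most serious events come from the illness. The difficulty is its overlap with the drug's own named harms. A patient recovering from critical illness may develop heart failure, ischaemia or a raised ALT from the illness, from nandrolone, or from both. A blinded investigator looking at one such patient has little basis for telling these apart. A comparison of counts between arms can show an excess, and during the trial the DSMB is the body placed to make that comparison.

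If the event is put down to the illness, the protocol does not require it to be reported as an SAE, and SAEs are what the DSMB is said to receive. What is at stake is whether the DSMB routinely sees the events for which individual attribution is weakest.

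**Working it through.** No arithmetic applies. The protocol gives no rate for cardiac events, ALT rises or hypertension, and no figure for how often investigators attribute them to the illness. The check is to follow one event through the text.

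1. **Is a new episode of heart failure or ischaemia inside the carve-out?** The protocol gives no list of expected complications. Harms describes organ failure in general terms as frequent and unrelated to the intervention, and heart failure can be read as falling under that. Nothing in the section says that a named safety endpoint is to be treated differently. The event may therefore be inside the carve-out, and the site decides.

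2. **Does the next sentence bring it back?** Yes, if the investigator thinks the drug may have contributed or is otherwise concerned. That is a low bar, but it is applied by someone who does not know the treatment. The sentence also does not say to whom the event is reported, or that an event reported under it then counts as an SAE.

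3. **What reaches the DSMB?** Interim analyses names SAEs. No section says that safety endpoints, adverse events not classed as SAEs, or deaths as such are sent to it. No analysis is scheduled at which they would be tabulated by arm.

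4. **Are the events captured elsewhere?** The safety endpoints are declared, so they are meant to be counted in both arms. The list under Data collection includes ICU, hospital and day-60 mortality. It includes ALT, but from routine tests timed by the treating clinicians. It has no item for cardiac events or blood pressure. The eCRF itself is not shown.

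5. **Which endpoints are affected?**

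| Safety endpoint | Plausible as a complication of critical illness | In the data list |
|---|---|---|
| Cardiac ischaemia or heart failure | Yes | No |
| ALT rise | Yes | Yes, from routine tests |
| New hypertension | Yes | No |
| Virilisation in females | No | No |

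The middle column is a judgement, since the protocol does not classify these events. On that judgement the carve-out hardly touches virilisation. The cardiac and ALT endpoints are the core, because the same section also lists them as possible effects of the drug.

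**The case against.** The case on the other side has real force.

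- **The reporting bar is low.** An investigator who cannot exclude nandrolone has met the test of potential causality, and the protocol itself lists these events as possible effects. This stands as a safeguard. It does not make reporting uniform, because a site that confidently blames the illness need not report.
- **The overlap is not spelled out.** No section names cardiac events as expected complications, and the exclusion criteria remove active cardiac disease and low ejection fraction, so a new cardiac event is harder to dismiss as background. This narrows the gap. It does not close it, because the carve-out is worded generally and sets no named event aside.
- **The DSMB can ask for more.** Its power to call for an analysis by arm is unrestricted and would reach endpoints and deaths. That stands. The power has no schedule, however, and the only stated information that might prompt its use is the SAE feed.
- **A charter may settle it.** The contents of DSMB listings are often fixed in a charter, and none is shown. But the carve-out and the SAE feed are both written into this protocol, and sites report under it.
- **The trial is small.** With 60 patients, about 30 per arm, even complete listings will seldom be conclusive. This limits the benefit but does not argue for withholding the listings.

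A reader might go further and infer that expected complications are exempt from SAE reporting, or that the DSMB receives nothing but SAEs. The text supports neither. It says that such events are not reported automatically, and it promises all SAEs without saying that nothing else will be sent.

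**Conclusion.** The point holds as a gap in the reporting pathway. For the named safety endpoints that resemble critical illness, the protocol does not say that they reach the DSMB by arm regardless of attributed cause, and it leaves their reporting as SAEs to blinded individual judgement. An imbalance may therefore not come to the DSMB routinely while the trial is running.

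It would go too far to infer that these events are lost, or that the DSMB is cut off from them. They are declared safety endpoints, due to be counted in both arms, and the DSMB can ask for them. What is uncertain is routine visibility during the trial. The efficacy analysis is not affected.

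The conclusion rests on three assumptions: that cardiac events, ALT rises and new hypertension can reasonably be read as expected complications of critical illness; that the DMC and the DSMB are the same body; and that no unseen charter already requires these listings. The frequency of such events and the share attributed to illness are unknown, so no number of unseen events can be given.

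**What to change.** - **Harms:** state that cardiac ischaemia or heart failure, ALT rise, new hypertension and all deaths are outside the carve-out. Keep the carve-out for other ICU complications.
- **Interim analyses:** state that these events are tabulated by coded arm for the DSMB whatever cause the investigator assigns.
- **Data collection:** add eCRF fields for the cardiac and blood pressure endpoints, which the present list does not contain.

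The cost is a sentence in each of the first two sections, a few eCRF fields, some extra event entries and one by-arm listing in a trial of 60 patients. The downside is that some non-serious events, such as isolated ALT or blood pressure findings, will appear in the DSMB listing. Only reporting changes; treatment and clinical management do not.

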#### **2.2.2 Exclusion criteria**

- 1.) Intercurrent septic shock (fevers, broad spectrum anti-microbials, and needing vasopressors)
2. Active cardiac disease (such as STEMI/NSTEMI in last 2 weeks) or EF <35%
3. Prostate or breast cancer
4. Ongoing reason for catabolic state (active malignancy, HIV & opportunistic infection last 2 months)

5. Unable to engage in rehabilitation (due to significant neurological or orthopaedic issues)
6. Normal age-related level of serum testosterone in males (measured in early morning 6-9am)
7. Pregnancy or breast-feeding
8. Any known allergies to nandrolone components – including peanuts and soya and latex.
9. Elevated LFTs (ALT > 5x normal) and impaired bilirubin excretion
10. Polycythaemia (Hb > 165 males, > 150 females)
11. Nephrotic syndrome.
12. Athletes competing in international/national events.
13. Expected death within the next week

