## **DATA COLLECTION, MANAGEMENT, AND ANALYSIS**

### **Data collection methods**

#### **Data Collection**

Data will be collected on a prespecified eCRF (RedCap - Research Electronic Data Capture - a secure web application for building and managing online surveys and databases) supported by a study-specific data dictionary and including checks of logical consistency and automatic query generation.

The following data will be collected:

- Age
- Gender
- ANZICS APD number

- Admission type (elective vs. emergency)
- ICU admission source (i.e. Emergency Department vs. ward vs. theatre vs. other hospital)
- Chronic APACHE co-morbidities
- APACHE-III admission diagnosis
- Illness severity based on the on the APACHE-II and III scores and risk of death, and “ANZ Risk of Death” models score
- ICU or HDA mortality
- ICU or HDA LOS
- Total duration of mechanical ventilation
- Total duration of vasoactive medication requirement
- Incidence and duration of renal replacement therapy
- Hospital mortality
- Post-ICU ward LOS
- Hospital disposition (home vs other acute care facility vs rehabilitation)
- ICU readmission
- Hospital readmission
- Day 60 mortality
- Inflammatory markers (CRP, Procalcitonin and WBC count at enrolment, ICU discharge and hospital discharge)
- BMI, weight at hospital admission, pre-admission medications.
- Baseline SF-36, FIM score and Barthel Index, to determine the patient’s pre-existing functional status (based on status two weeks prior to admission to ICU, from patient or surrogate).
- **Measurement of variables:**
  - **1. Laboratory tests**
    - Pregnancy test in women of child bearing age
    - Baseline: sex hormone binding globulin, testosterone.

- Routine blood tests will occur as planned by treating clinicians, and will collect:
- Haemoglobin, white cell count, albumin, urea and creatinine, alanine transferase.
- Lipids at baseline and at day 15-21.
- **2. Strength and weight measurements**
- a) Weekly: Hand grip strength, weight (kg) and MRC.
- **3. Other measures**
- Physiotherapy received - Duration of rehabilitation physiotherapy and mobility achieved (ventilation physiotherapy treatments will not be counted).
- Nutrition received - Caloric intake (kcal/total), Protein intake (g/total), Food intake (% of meals).
- **Follow-up**
- Phone call follow-up at 3 & 6 months using the SF-36 score , and asking about return to work (see script page).

*Pre-specified Subgroups:*

BMI at enrolment < 20

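### Polycythaemia is a named side effect with no safety endpoint, and no post-dose time is fixed for haemoglobin or ALT

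*Protocol*

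**What the plan says.** The Harms section of the protocol gives six potential side effects. The last three are "abnormal LFTs, Polycythaemia, Increased sensitivity to oral anticoagulants". The next sentence opens the endpoint list with "Safety endpoints include: new onset hypertension" and goes on to "abnormal liver function tests (ALT increase > 100% from baseline and >100", cardiac ischaemia or heart failure, and virilisation in women. Nothing in that list is based on haemoglobin.

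Section 2.2.2 excludes patients with "Polycythaemia (Hb > 165 males, > 150 females" and patients with "Elevated LFTs (ALT > 5x normal) and impaired bilirubin excretion". The section on allocation concealment makes randomisation wait until every eligibility criterion is met.

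Under Data Collection, haemoglobin and ALT fall under this rule: "Routine blood tests will occur as planned by treating clinicians". Other blood markers in the same section have set times. One entry reads "Lipids at baseline and at day 15-21", and CRP, procalcitonin and white cell count are due at enrolment, ICU discharge and hospital discharge. Follow-up after discharge is by telephone.

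**The concern.** Two adjacent sentences in Harms do not match. Polycythaemia is expected from the drug, is serious enough to exclude patients, and already has a numerical definition. Once dosing starts, however, no endpoint counts it.

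The ALT endpoint is a change from baseline, so it exists only for patients with a later ALT. The protocol does not say when that value is taken. How complete the endpoint is then depends on local ordering habits and on length of stay, and length of stay is itself an outcome that the drug is meant to shorten. A laboratory rise that nobody measures in hospital cannot be recovered by a telephone call.

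At stake is the safety comparison in a trial of 60 patients, about 30 per arm at 1:1 allocation, where each missed event matters.

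**Working it through.** The plan states no figure on this point, so there is none to reproduce. The check has two parts.

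**1. Side effects, endpoints and sampling times set side by side**

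- Polycythaemia: side effect, yes; numerical definition, yes (Section 2.2.2); safety endpoint, no; fixed post-dose time for haemoglobin, no.
- Abnormal liver tests: side effect, yes; safety endpoint, yes (ALT); fixed post-dose time for ALT, no.
- Lipids, CRP, procalcitonin, white cell count: used by no listed safety endpoint; fixed times, yes.
- Baseline: the ALT and haemoglobin exclusions cannot be applied without both values, and randomisation waits for eligibility. A baseline is therefore implied for both tests, and the gap is post-dose only.

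**2. How far a shorter stay could change detection**

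Inputs from the protocol: planned stays of 26 and 23 days, and pilot stays of 26 and 36 days, both from the sample size section. That section does not label the pilot arms, so I take the shorter stay as nandrolone.

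Assumptions, not in the protocol: enrolment on hospital day 5 or 10; a laboratory change that is present from 7 days after enrolment until discharge; tests at a constant random rate; every patient staying for the stated number of days.

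Window = stay - enrolment day - 7. For 26 and 23 days this is 14 and 11 days (enrolment day 5) or 9 and 6 days (enrolment day 10). With r tests per week:

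P(at least one test) = 1 - exp(-r × window / 7)

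Example, r = 1 and day 10: 1 - exp(-9/7) = 0.724 and 1 - exp(-6/7) = 0.576.

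| Tests per week | Enrolment day 5: 26 vs 23 days | Enrolment day 10: 26 vs 23 days |
|---|---|---|
| 0.5 | 63% vs 54% | 47% vs 35% |
| 1 | 87% vs 79% | 72% vs 58% |
| 2 | 98% vs 96% | 92% vs 82% |
| 7 | about 100% in both | about 100% in both |

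With the pilot stays (36 vs 26 days) and one test a week, the figures are 97% vs 87% (day 5) and 93% vs 72% (day 10).

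If the true event rate were equal in the two arms, the ratio of detected events (shorter stay to longer stay) would be 0.576/0.724 = 0.80 at one test a week with enrolment on day 10, and 0.957/0.982 = 0.97 at two tests a week with enrolment on day 5. In counts, an assumed 10% rate in 30 patients per arm at one test a week and day 10 gives 30 × 0.10 × 0.724 = 2.2 detected events against 30 × 0.10 × 0.576 = 1.7.

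**The case against.** The strongest reply is that little will be missed in practice. The endpoint list is introduced as inclusive, haemoglobin is collected anyway, and adverse events judged potentially related must be reported. ICU patients are bled often, and the promised procedures manual could set sampling times.

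Part of this stands. A comparison of haemoglobin by arm remains possible; it is only not named in advance. Frequent testing removes most of the difference between arms, as the table shows. The rest does not close the gap. A laboratory abnormality must be measured before anyone can judge its cause, and Harms itself warns that abnormal laboratory values are common in these patients. Dosing can run to three weeks, so some of it may fall on the ward, where no test frequency is set. The protocol itself fixes times for other blood markers, so the timing of a test that a safety endpoint needs belongs beside them.

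Some stronger readings are tempting but not supported:

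- *No baseline exists.* The eligibility criteria imply one for both tests.
- *Lipids are the only scheduled post-dose sample.* CRP, procalcitonin and white cell count are also due at ICU and hospital discharge.
- *Harms on nandrolone will be under-counted.* This needs both a shorter stay and sparse testing. Dosing also ends at discharge, so fewer events in that arm could reflect fewer doses.
- *Anticoagulant sensitivity should also become an endpoint.* It too has no match in the list, but the protocol collects neither INR nor in-hospital anticoagulant use. That would be new data collection and is not part of this point.

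**Conclusion.** The point holds in a limited form. One named drug harm with a ready definition has no safety endpoint, and the ALT endpoint rests on a post-dose value whose timing is not set. Both follow from the text alone and need no assumption.

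Differential detection is a possibility, not a demonstrated bias. For the planned stays, the difference in the chance of a test runs from nil with daily testing to about 15 percentage points at one test a week with enrolment on day 10. It rests on the assumed enrolment day, test rate and timing of the laboratory change. At the assumed 10% event rate, the 15-point case is about half an event per 30 patients (2.2 against 1.7).

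A reader might also compute the chance of seeing any event on nandrolone. At an assumed 5% rate it is 1 - 0.95^30 = 79% with full capture and 1 - 0.975^30 = 53% with half captured. The arithmetic is right, but it describes one arm under an assumed capture share and says nothing about a difference between arms.

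**What to change.** - In Harms, add to the safety endpoints a new haemoglobin value above the sex-specific cut-offs of Section 2.2.2. Patients above them at entry are excluded, so the definition needs no further work.
- In Data Collection, add haemoglobin and ALT to the blood samples already scheduled at enrolment and at hospital discharge, identically in both arms. The enrolment sample gives the ALT endpoint a dated baseline.
- Add both tests to the day 15-21 lipid sample for patients still in hospital. This sample should not stand alone. If the days count from enrolment and enrolment is on hospital day 5 to 10 (assumed), it falls on hospital day 20 (5 + 15) to 31 (10 + 21). Planned median stays are 23 and 26 days, so many patients would have left, more of them in the arm with the shorter stay.
- Report each laboratory endpoint by arm with the number tested and the time from first dose to sample. The statistical section already promises numbers at risk by group; this states what at risk means for a laboratory endpoint and lets a reader see differences in follow-up or exposure.

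The cost is a haemoglobin and an ALT assay on samples already drawn, and one more row in the safety table. No dose, eligibility rule or treatment decision changes.

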## **ETHICS AND DISSEMINATION**

### **Research ethics approval**

All research ethical and regulatory approvals will be sought and obtained at each site from the responsible local and/or national human research ethics committee in accordance with National and State Requirements prior to the start of the study. The study has been designed in a manner to ensure that the welfare of participants is protected at all times and that respect for their autonomy is demonstrated through appropriate mechanisms of consent.

### **Protocol amendments**

Protocol amendments will be updated on relevant clinical trial registries by the Project Manager. Amendments will be communicated by regular newsletters, teleconferences, and emails to site Principal Investigators and Research Co-ordinators.

## **Consent**

The majority of patients enrolled in this trial will have capacity to give consent at the time of trial enrolment. The following consent options are acceptable: (i) consent by the patient (ii) consent by a substitute decision maker using the IMP / GAA pathway for WA Health; (iii) Delayed consent from the patient. All participants who recover sufficiently will be given the opportunity to provide informed consent for ongoing study participation and for the use of data collected for the study.

## **Confidentiality**

Patients will be allocated a unique study number. The site research co-ordinator will compile an enrolment log that includes the patients' details and a unique study number. Study data will be obtained from the patients' medical records. The study data and the study enrolment logs will be kept separately. Contact details for participants and their next of kin will be provided to the Project Manager and quality of life outcome data will be obtained by a research coordinator by phoning participants and/or their next of kin.

